### Research questions

The following research questions are posed:Will music therapy (TMI) be as effective as standard treatment regarding the decrease of TSD symptoms (primary outcome) from pre to post treatment and from pre-treatment to 6 months’ follow-up?Will music therapy (TMI) be as effective as standard treatment regarding the decrease of dissociation and the improvement of attachment style and well-being (secondary outcomes) pre to post treatment and from pre-treatment to 6 months’ follow-up?Does any variable from the patient data at baseline (i.e., gender, age) specifically correlate with good outcomes of music therapy on trauma symptoms compared to standard treatment?Concerning patient satisfaction with therapy sessions, is there a difference between music therapy and verbal therapy, and is there any development in the assessment of the sessions during the therapy course?Will basic levels of salivary oxytocin, beta-endorphin and substance P be changed by the treatment, are any changes stable at follow-up, and are there differences between the two groups?Will the levels of salivary oxytocin, beta-endorphin and substance P be affected by one session, and are there a difference between the groups, and between a session at the beginning and in the end of treatment?

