#### Hypotheses

The hypotheses of the study are that music therapy (TMI) will not be less effective than verbal psychotherapy according to the principle of clinical equipoise, and that we will see a decrease in PTSD symptoms and dissociation as well as an increase of well-being and improvement of safe attachment style after both music therapy and standard treatment. Furthermore, we hypothesize that patient evaluation will be equally positive with regard to both treatment conditions. According to salivary hormones the hypotheses are, that music therapy will be no less effective than verbal therapy regarding increase of basic and session levels of oxytocin and decrease of basic and session levels of beta-endorphin and substance P.

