### Secondary outcomes

The secondary outcomes assess changes in attachment and dissociation, both factors have been associated with PTSD and Complex PTSD, playing a role for the therapeutic alliance, relational capacities and ongoing development of integrative capacity in the patient. The Revised Adult Attachment Scale (RAAS) [75] is a revision of the original Adult Attachment Scale evaluating the experience of emotional closeness or distance with 18 questions which are answered on a Likert scale with 5 points ranging from “right for me” to “not at all right for me.” The questionnaire indicates whether a person has a predominantly safe, defensive/anxious or dependent attachment style. Safe attachment measured with RAAS correlates negatively with the PTSD diagnosis [76].

Two dissociation scales are included in the study. The Dissociative Symptoms Scale (DSS) [77] evaluates moderate to severe levels of depersonalization, de-realization, gaps in awareness or memory, and dissociative re-experiencing. The DSS is applied with the permission from the developers. The 20 questions are answered in relation to the amount of time that the person experiences each symptom on a 5-point Likert scale ranging from “not at all,” “once or twice a day” to “more than once a day.” The scale shows good psychometric properties [77].

The Somatoform Dissociation Questionnaire (SDQ-20) [78, 79] is a supplementary scale for the evaluation of somatic dissociation, but going a little more in depth. The 20 questions ask about dissociative symptoms that are evaluated on a 5-point Likert scale, ranging from “does not at all fit with me” to “fits extremely well with me.” If an item is acknowledged as fitting for the person, there is an additional question to whether a physician has provided a physical diagnosis that explains the symptom or not. The scale has good psychometric properties and has been found to correlate with self-reported traumatization [78, 80].

The WHO Well-being-5 (WHO-5) is a short form that allows information of general health and absence of distress to appear [81]. The scale consists of five questions measuring quality of life and well-being (joy, energy, healthy rest, motivation and meaningful activities).

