#### Statistical methods

Statistical analysis will be carried out in the statistical environment R [82] in cooperation with the statistical department in the research unit of Region Zealand and PFI Region Zealand (Production, Research and Innovation Unit). Data will be treated according to the intention-to-treat principle. Analysis of all data will take place after the conclusion of data collection. Following the initial screening of the data significance tests concerning differences between standard treatment and music therapy will be carried out in order to assess the non-inferiority of music therapy. Significance and variance for the primary outcome measure will be calculated with analysis of covariance (ANCOVA), including data from five measuring points. Secondary questionnaire outcome data will also be calculated with ANCOVA, using three data points. Correlations between trauma symptoms, attachment, dissociation and demographic parameters are investigated. A regression analysis will be applied to look for predictors of improvement of trauma symptoms (HTQ) and change of attachment style, as well as predictors for improvement connected to treatment (music therapy or standard treatment). Analysis of hormones will be split up in an ANCOVA testing variance between groups and with time (baseline to follow-up), and simple significance tests of change after single sessions (between the third and 14th session and between the interventions). Session satisfaction data will be treated with descriptive statistical methods.

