#### Power calculation

In order to estimate the level of power we reviewed randomized and non-randomized trials where refugees suffering from PTSD were treated with stabilization and trauma exposure strategies with cognitive and narrative elements corresponding to the standard treatment in our study, and where the Harvard Trauma Questionnaire was used to measure changes in trauma symptoms (the primary outcome in the current study). The variations in the studies were considerable, and we chose to only look at studies that had a number of sessions that were similar to the current study, and where the mean baseline value of HTQ were around 3.3, a value that we found to correspond to our population in the pilot study [18, 62, 83–86]. Non-significant differences between 0.1 and 0.5 was found in HTQ from pre to post treatment. Based on our clinical experience and data from these studies, we estimate a clinical insignificant difference of 0.3 as the maximal difference between music therapy and standard treatment to confirm the non-inferiority hypothesis. A mean standard deviation of 0.48 on post-scores of HTQ was calculated from the studies referred above.

The power calculation was based on a significance level of 0.05, power 0.08, *d* = 0.3 and *SD* = 0.48. The calculation was carried out with software from Epi-info 7 (http://wwwn.cdc.gov/epiinfo/) in cooperation with Department for Statistics, Psychiatric Research Unit, Region Zealand and PFI.

The result indicates a minimum of 64 participants (32 in each group).

Adherence to music therapy has been found to be good in psychiatric patients with a low dropout rate (11.5%) [87]. In three former randomized clinical studies on psychological treatment of refugees with large samples low dropout rates (7–10%) were demonstrated at follow-up [21, 83, 88].

We have, therefore, chosen to include a dropout rate of 10% and thus end up with *n* = 70 (35 in each group).

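### Research question 2 asks whether music therapy is as effective on four secondary scales, but the only margin is in HTQ points, so a non-significant difference would have to serve as the answer

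*Protocol article*

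**What the plan says.** Trial design places the trial in a non-inferiority framework, and Hypotheses expects that "music therapy (TMI) will not be less effective than verbal psychotherapy".

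Research questions puts the same comparative question twice. Question 1 concerns trauma symptoms, the primary outcome. Question 2 asks whether music therapy will be "as effective as standard treatment regarding the decrease of dissociation and the improvement of attachment style and well-being (secondary outcomes", and fixes two time points: "secondary outcomes) pre to post treatment and from pre-treatment to 6 months’ follow-up".

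The Secondary outcomes section supplies the scales. For attachment it is the RAAS: "The questionnaire indicates whether a person has a predominantly safe, defensive/anxious or dependent attachment style". For dissociation, "Two dissociation scales are included in the study": the DSS and the SDQ-20, the latter of which "is a supplementary scale for the evaluation of somatic dissociation". For well-being it is the WHO-5.

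Only one margin appears, under Power calculation: "we estimate a clinical insignificant difference of 0.3 as the maximal difference between music therapy and standard treatment". That paragraph concerns the HTQ alone, and the SD of 0.48 beside it is also an HTQ figure.

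Statistical methods says that non-inferiority will be assessed through significance tests of differences between the two treatments. For the other scales it adds: "Secondary questionnaire outcome data will also be calculated with ANCOVA, using three data points".

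**The concern.** A claim that one treatment is as effective as another needs a stated amount of loss that would still be tolerated. For the HTQ that amount is given. For DSS, SDQ-20, RAAS and WHO-5 it is not, and 0.3 HTQ points cannot be carried over to instruments with other items, ranges and SDs.

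The method that is stated does not fill the gap. A significance test of a difference asks whether the data rule out equality, not whether they rule out a relevant deficit. Where a margin exists, such a test can be read as a test against that margin. Where none exists, the only way left to answer question 2 affirmatively is to find no significant difference. That outcome becomes easier to reach as the data become noisier or fewer.

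At stake is a published statement that music therapy matches verbal therapy on dissociation, attachment or well-being when a substantial deficit has merely gone undetected. The article describes the trial as a guide to the choice between the two treatments, so such a statement could influence referral.

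**Working it through.** **Inputs.** From Power calculation: margin 0.3, SD 0.48, significance level 0.05 (sidedness not stated), 32 per group before dropout. Power is printed as 0.08 and read here as 0.80. From Research questions and Secondary outcomes: four scales, two time points. No margin, SD or power basis is given for any secondary scale.

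**Step 1. Reproduce the plan's figure.** n per group = 2 × (SD/margin)² × (z for alpha + z for power)².
- One-sided 0.05, power 0.80: 2 × (0.48/0.3)² × (1.645 + 0.842)² = 2 × 2.56 × 6.18 = 31.7, so 32 per group and 64 in total. This matches the article.
- Two-sided 0.05: 2 × 2.56 × (1.960 + 0.842)² = 40.2, so 41 per group and 82 in total. This does not match.

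The sample size is therefore that of a one-sided 5% non-inferiority test on the HTQ. Nothing in it refers to another scale.

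**Step 2. Standardize the HTQ margin.** 0.3/0.48 = 0.625 SD. Using this value on another scale is an assumption made only for illustration.

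**Step 3. Chance that a real deficit is non-significant.** For a true deficit of d SDs and n = 32 per group, the non-centrality is d × √(n/2) = d × 4. The chance of missing it is the probability that a non-central t with 62 degrees of freedom falls between −1.999 and +1.999 (two-sided 5%).

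| True deficit | Non-centrality | Missed, t distribution | Missed, normal approximation |
|---|---|---|---|
| 0.5 SD | 2.0 | 49.6% | 48.4% |
| 0.625 SD | 2.5 | 30.8% | 29.5% |

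**Step 4. Sensitivity.** Each assumption is changed on its own.
- All 35 per group analysed (t distribution): non-centralities 0.5 × √17.5 = 2.09 and 0.625 × √17.5 = 2.61; missed 46% and 27%.
- One-sided 5% test towards a deficit (normal approximation): Φ(1.645 − 2.0) = 36% and Φ(1.645 − 2.5) = 20%.
- Baseline adjustment, with the deficit in raw SDs and an assumed baseline correlation of 0.5: the residual SD is √(1 − 0.25) = 0.866 of the raw SD, so the non-centralities become 2.0/0.866 = 2.31 and 2.5/0.866 = 2.89. By the normal approximation, Φ(1.96 − 2.31) = 36% and Φ(1.96 − 2.89) = 18% are missed.

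Across these cases a 0.5 SD deficit is missed in 36% to 50% of trials and a 0.625 SD deficit in 18% to 31%, for each comparison.

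**The case against.** The strongest reply is that this is a condensed article. Margins, an order of testing and alpha rules for secondary outcomes commonly belong in the full protocol or the SAP, which are not shown. The article does name one primary outcome, labels the others secondary, calls the SDQ-20 supplementary and reserves the exploratory label for the saliva peptides. In Hypotheses, the clause on not being less effective names no secondary scale. The secondary scales appear there only as expected to improve after both treatments. A research question is also not a success criterion.

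Most of this stands, and it limits the point. A reader might infer that the plan lacks any ranking of outcomes, tests each scale separately at full alpha, and so carries a large chance of some false claim over eight comparisons. The text does not support that. The ranking into primary, secondary and exploratory is there. No alpha is stated for the secondary scales. An ANCOVA on three data points may be one model per scale, so the count of eight is a construction from four scales and two visits. A false non-inferiority rate cannot be worked out for scales without margins, and a calculation that requires success on every scale would use a rule the article never sets. An unstated order among secondary outcomes is no finding here.

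The reply does not reach what the article itself fixes. It puts the comparative question for these scales in the same terms as for the HTQ, inside a non-inferiority framework, and names difference testing as the way to assess non-inferiority. That pairing of claim and method is stated, not omitted.

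**Conclusion.** The point holds in this form: question 2 has no criterion of its own, and the stated method would let a non-significant difference stand as evidence of equal effectiveness. With 32 per group and a two-sided 5% test, a true deficit of 0.5 SD goes undetected about half the time and one of 0.625 SD about 31% of the time.

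These figures assume normal outcomes, equal groups, the deficit expressed in the SD left after any covariate adjustment, and 32 analysed per group. The 0.625 SD is borrowed from the HTQ and is not a proposed margin for any other scale. The numbers at 6 months may be smaller, because participants who need additional psychotherapy are excluded from follow-up.

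A reader might go further and infer that a secondary result is meant to stand in for a failed HTQ result. Nothing in the article says so. The consequence is limited to the conclusions drawn on the secondary scales. It deserves correction because the correction is cheap.

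**What to change.** In Research questions and Statistical methods, state that non-inferiority is concluded for the HTQ only. Reword question 2 to ask how the two treatments compare on dissociation, attachment and well-being. Report DSS, SDQ-20, RAAS and WHO-5 as supportive: an adjusted mean difference with its 95% confidence interval at post-treatment and at 6 months, and no conclusion that music therapy is as effective or non-inferior on any of them.

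If one secondary claim is wanted, fix a single scale, a single time point and a justified margin on that scale before unblinding, and test it only once HTQ non-inferiority has been met.

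The cost is a wording change in the protocol and SAP, with no new data and no extra patients. The article says data stay concealed until the trial is complete, so the change could be made without knowledge of results. The price is that statements of equal effectiveness on the secondary scales can no longer be offered as conclusions.

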#### Hypotheses

The hypotheses of the study are that music therapy (TMI) will not be less effective than verbal psychotherapy according to the principle of clinical equipoise, and that we will see a decrease in PTSD symptoms and dissociation as well as an increase of well-being and improvement of safe attachment style after both music therapy and standard treatment. Furthermore, we hypothesize that patient evaluation will be equally positive with regard to both treatment conditions. According to salivary hormones the hypotheses are, that music therapy will be no less effective than verbal therapy regarding increase of basic and session levels of oxytocin and decrease of basic and session levels of beta-endorphin and substance P.

### Trial design

The research design is a randomized clinical trial with a parallel-group design including two intervention groups: music therapy (Trauma-focused Music and Imagery (TMI)) and standard psychological treatment. We use a non-inferiority framework, where we test whether or not music therapy is inferior to standard treatment. We intend to allocate 70 adult refugees diagnosed with PTSD. Repeated measures take place at baseline, post therapy and at 6 months’ follow-up. A short form of the primary outcome measure is also collected twice during the treatment period (session 5 and 10). Session evaluation from clients is collected after each session. Saliva samples are collected at baseline, post therapy and follow-up, and also pre and post sessions 4 and 14 (see the Standard Protocol Items: Recommendations for Interventional Trials (SPIRIT) flow chart; Fig. 1). All dimensions of the study protocol have been described adhering to the SPIRIT Checklist (Additional file 1). We also adhere to the revised Consolidated Standards of Reporting Trials (CONSORT) guidelines [63].

**Fig. 1 Fig1:**
[figure not shown]
Schedule of enrollment, interventions, and assessments (Standard Protocol Items: Recommendations for Interventional Trials (SPIRIT) flow chart)

### Setting

The study is carried out in the outpatient Trauma Clinic for Refugees under the Department of Special Functions in Psychiatry, Region Zealand, Denmark. The clinic offers treatment in three units placed at different locations in the area a multidisciplinary treatment including a combination of medication, psychotherapeutic treatment, social counseling, health advice given by nurses, body therapy and music therapy. Translators are used as needed. Around 250–300 patients are referred per year, most from general practitioners and some from the Centers of community psychiatry. Patients must have a residence permit to access the clinic. The average treatment time is 4–6 months. When a patient is referred to the clinic without a PTSD diagnosis, the physician and psychologist assess the patient. As part of the visitation and screening procedure in the clinic, the physician and the treatment team estimate a mentalization level (small, medium or high) for the patient, based on the actual psychosocial resources and capacity for introspection, reflection, affect regulation and empathy [64, 65].

The trial covers all three locations of the clinic. A list of the places can be found in the Appendix. Four psychologists and four music therapists are responsible for the treatment.

### Participants

The participants are adult refugees (age 18–67 years) accepted for treatment by the Clinic of Traumatized Refugees, i.e., by way of having a psychic trauma related to war, persecution, torture, etc. Diagnoses for inclusion are: PTSD (ICD-10: F43.1 or DSM-IV-TR: 309.81), Enduring personality change after catastrophic experience (ICD-10: F62.0), or Complex PTSD/DESNOS (Disorders of Extreme Distress Not Otherwise Specified) (DSM-V). Comorbidity, such as depression, anxiety disorders, non-psychotic depression, episodic psychotic symptoms related to (Complex)PTSD, somatoform disorders or personality disorders, are accepted in the study.

Medication for PTSD and comorbid illness as well as for somatic diseases are accepted. The participants can be refugees or family united with refugees from all countries. Included are Arabic-, English- or Danish-speaking participants. These criteria are chosen to secure access to self-report questionnaires in a language understood by the participants, thereby avoiding misinterpretation of the questions. Included in the study are participants with a medium to high mentalization level (as estimated in the clinic after the visitation procedures). All participants receive verbal and written information in their native language and are included after giving informed consent to participate in the study.

#### Exclusion criteria

Exclusion criteria are severe psychotic disorders, defined as psychotic disorders in the domain of F2 and F3 in ICD-10. No active abuse was accepted (ICD-10 F10.24–F10.26), and persons requiring hospitalization are not included. Patients with suicidal risk at referral are not included in the study.

#### Eligibility criteria for psychotherapists

Psychologists carrying out standard treatment in the study are employed as psychologist in the Clinic for Traumatized Refugees; the music therapists have to have a master’s degree in music therapy and/or be a certified GIM therapist, and be employed in the clinic.

### Recruitment

The visitation procedure of the Trauma Clinic for Refugees includes: consultation with a physician regarding diagnostics, medication and motivation for treatment, consultation with a nurse to obtain information about health, consultation with a psychologist to obtain an overall record of trauma history and background, coping strategies and attachment style. Assessment of biopsychosocial competencies and mentalization level are carried out by the cross-disciplinary team at conferences.

#### Procedure of obtaining informed consent

Following the regulations of the regional Ethical Scientific Committee, patients eligible to participate in the trial are invited to an information meeting with one of the music therapists or the senior staff specialist, where they are informed orally as well as provided with a written description of the study and of their rights as participants that is available in Arabic, Danish and English. A translator is present to translate if necessary, and the patient is allowed to bring a companion. The meeting takes place in calm surroundings, and there is time set aside for questions. The patient is given information about the purpose of the project, the content, pros and cons for participants, and their rights as a participant in a scientific health study. The principle of randomization is explained, and both treatment options are described, so that the participants only give informed consent when understanding their options. The patient is given information about their right to withdraw from the study at any time without missing out on options for current and future treatment. The patient is informed that they will be informed if important health issues are revealed during the study, unless they do not want to receive this information, and that at anytime they can ask for sight of their personal data and withdraw such data from the project. The patient gives permission for the data to be analyzed and published anonymously. The patient is given one week to consider before giving informed consent. If the patient gives consent directly after the information, they sign the informed consent on the spot. If the patient needs time to consider their participation a telephone call is scheduled a week later, and a new meeting is set up for the signing procedure.

A participant is included in the study when we have obtained informed content. The leader of the study and the patient each have a copy of the informed consent contract (see Additional file 2).

